**7.6.2.2 Immunogenicity**

**7.6.2.2.1 Prime immunization**

The main results of the immunogenicity analysis for the prime immunization will be based on the I-PPE population. The I-PPS will also be analyzed. Particularly, post-infection immunogenicity data for SARS-CoV-2 infection will be excluded from analysis, and pre-infection data may still be included. Exploratory analysis will also be performed on participants who are infected at baseline (positive for nucleic acid or antigen tests).

The GMT of neutralizing antibody against SARS-CoV-2 (including variants or mutant subtypes) in the immunogenicity subgroup at each time point post vaccination is analyzed by the covariance model. The model is constructed with antibody GMT post vaccination after logarithmic transformation at each time point as the dependent variable, antibody GMT before vaccination after logarithmic transformation at each time point as the covariate, the age (18–59 years,  $\geq 60$  years), the vaccine type of the last previous dose (inactivated, non-inactivated), and the group as fixed effects. The arithmetic mean of antibody post vaccination after logarithmic transformation at each time point in each group and the least squares mean (LSM) of the difference between groups are calculated according to the model; after inverse logarithmic transformation, the LSM and 95% confidence interval of antibody GMT and GMT ratio (test group / control group) at each time point post vaccination in each group are calculated.

The geometric mean and two-sided 95% confidence interval are used to statistically describe anti-SARS-CoV-2 neutralizing antibody GMT and GMI at each time point in the test group and the control group under the immunogenicity subgroup, respectively.

The seroresponse rates of anti-SARS-CoV-2 neutralizing antibody in the test group and control group at each time point post vaccination are calculated, respectively, and their 95% confidence

intervals are calculated by Clopper-Pearson method. The ratio difference (test group - control group) and its two-sided 95% confidence interval are calculated using the CMH- $\chi^2$  test including randomization stratification factors, and the difference between groups is statistically tested.

The histogram of anti-SARS-CoV-2 neutralizing antibody titer in the test group and the control group under the immunogenicity subgroup in the prime immunization, the forest plot of anti-SARS-CoV-2 neutralizing antibody GMT in each subgroup, and the forest plot of anti-SARS-CoV-2 neutralizing antibody seroresponse rate in each subgroup are drawn, respectively.

#### **7.6.2.2.2 Persistence study**

The immunogenicity analysis for the persistence will be based on subgroups of I-PPE that participate in the immune persistence study. The visits to be analyzed include scheduled visits on Days 7, 14, 28, 90, and other dates post vaccination until the end of the study.

GMT and two-sided 95% confidence interval are used to statistically describe anti-SARS-CoV-2 neutralizing antibody in the test group and the control group under the immunogenicity subgroup, respectively. An ANCOVA model similar to that used for the prime immunization will be used for comparison between groups.

The serum positive rates of anti-SARS-CoV-2 neutralizing antibody in the test group and control group at each time point for the persistence study are calculated, respectively, and their 95% confidence intervals are calculated by Clopper-Pearson method. Differences between groups are statistically tested using CMH- $\chi^2$  test including randomization stratification factors.

The trend chart of anti-SARS-CoV-2 neutralizing antibody titer over time in the test group and control group during the persistence study are plotted, respectively.

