| Study Design | 
SCT had initiated several clinical trials to evaluate the safety and immunogenicity of SCTV01E and SCTV01C, including one Phase III immunogenicity trial for SCTV01E and SCTV01C and three Phase I/II trials for SCTV01C. SCTV01E and SCTV01C were manufactured by the same platform, sharing the same process, similar molecular characteristics and clinical dosage, therefore, these trials provide sufficient supportive safety and immunogenicity clinical data prior to the start of this Phase III trial for SCTV01E. The details of these trials are summarized in the investigator's brochure.
 
The dose strength of SCTV01E is 30<math>\mu</math>g (5/5/5/15<math>\mu</math>g for TM22/TM23/TM28/TM41)/dose based on the nonclinical and clinical study of SCTV01E and SCTV01C.
 
The study is a randomized, double-blind, placebo-controlled Phase III study. It will evaluate the protective efficacy and safety of SCTV01E against COVID-19 in participants who were previously vaccinated with primary series of COVID-19 vaccines and /or received booster vaccination.
 
The study design is shown in Figure 1.
 
Approximately 10,000 participants who were previously vaccinated with the primary series of COVID-19 vaccine and/or received booster
 |

vaccination and aged  $\geq 18$  years old will be enrolled. The exact number of participants enrolled in the study will depend on the infection rate of COVID-19 infection at the time of enrollment and the true vaccine efficacy of SCTV01E. If the attack rate is much higher, case accrual would be expected to be more rapid, enabling the study's primary endpoint to be evaluated much sooner, and the actual enrolled sample size may be less than planned.

A percentage of 5%~10% participants in the full analysis set will be set for both immunogenicity test and efficacy evaluation. (No limitation for the type of COVID-19 vaccine previously received or age ranges).

Participants will be randomly assigned to receive one dose of SCTV01E or placebo (normal saline) in a ratio of 1:1 on Day 0.

Participants are stratified by age (18-59 years,  $\geq 60$  years), the type of the last dose of COVID-19 vaccine previously received (inactivate, non-inactive) and region (study site).

Participants aged between 59 years to less than 60 years old will be taken as 59 years old;

[figure not shown]

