**Efficacy follow-up:**

Follow-up of protective efficacy will be started after the study vaccination. All participants will be asked whether they have any signs/symptoms related to COVID-19 by phone call, short message, email or other contacting methods once a week. The frequency of the efficacy follow-up may be adjusted according to the process of the study. Meanwhile, the participants could spontaneously report any COVID-19-related symptoms at any time during the study period. SARS-CoV-2 RT-PCR test will be performed if participants have signs/symptoms related to COVID-19. If participants meet the criteria for symptomatic infection of SARS-CoV-2 for the primary study endpoint, the virus will be isolated from the nasal/nasopharyngeal/throat swab and viral sequencing will be performed to identify the SARS-CoV-2 variants. Endpoint Adjudication Committee (EAC) will be set up in this phase III study to conduct independent evaluation and judgment for each case, to ensure a more accurate determination of the positive cases.

**Immunogenicity follow-up:** Participants in the immunogenicity subgroup will be sampled on Days 0 (before study vaccination), 14, and 28. 200 participants in the immunogenicity subgroup will be sampled on Days 7, 90, 180 and 365 for nAb of SARS-CoV-2 (including variants and subvariants).

**Safety follow-up:** All participants will be observed at site for at least 30 minutes after the study intervention. Both active monitoring and spontaneous reporting will be used. Solicited AEs within 7 days after the study vaccination and unsolicited AEs within 28 days after the study vaccination will be collected through vaccination record cards (VRCs).

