|                           | 
this upper limit, on the contrary, the participants will be sampled during screening period without waiting for the result before enrollment;
 
 
5. The participant and/or his/her legal guardian and/or his entrusted person can read, understand, and fill in record cards;
 
6. Healthy participants or participants with pre-existing medical conditions who are in stable condition. The “pre-existing medical conditions” include but are not limited to hypertension (systolic/diastolic pressure <math>\leq 155/100</math> mmHg), diabetes, Chronic cholecystitis and cholelithiasis, and chronic gastritis that meet the described criteria. A stable medical condition is defined as disease not requiring significant change in therapy or no need for hospitalization as a consequence of worsening disease state for at least 3 months prior to enrollment;
 
7. Fertile men and women of childbearing potential voluntarily agree to take effective contraceptive measures from signing ICF to 6 months after the study vaccination; the pregnancy test results of women of childbearing potential are negative on screening.
 
 |
| Exclusion Criteria | 
A participant who conforms to any of the following criteria should be excluded from the study:
 
 
1. A positive result of nucleic acid test or rapid antigen test for SARS-CoV-2 during the screening period;
 
2. Known history of SARS-CoV-2 infection (including asymptomatic and symptomatic infection of SARS-CoV-2) in the past 6 months before the study vaccination;
 
3. Presence of fever within 3 days before the study vaccination (<math>\geq 37.3^{\circ}\text{C}</math>);
 
4. A history of allergic reactions to any vaccines or drugs, such as allergy, urticaria, severe skin eczema, dyspnea, laryngeal edema, and
 
                                                                                                                                                                                                                                                                                                                                                                                                                                                                                                |

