**Immunogenicity evaluation:** Blood samples will be collected on Day 0 (pre-vaccination), Day 14 and Day 28 from participants in the immunogenicity subgroup (approximately 5%–10% of randomized participants), of which 200 participants need to undergo additional scheduled sampling on Day 7, Day 90 and other longer periods (detailed in the visit flow chart of the protocol) for the detection of SARS-CoV-2 (including mutant strains and mutant subtype) neutralizing antibody.

**Safety evaluation:** All participants will be observed at the study site for at least 30 minutes after the study intervention. Information is collected through a combination of active surveillance and spontaneous reporting. Solicited adverse events (AEs) within 7 days after vaccination and unsolicited AEs within 28 days after vaccination will be collected via vaccination record cards (VRCs). Serious adverse events (SAEs) and adverse events of special interest (AESIs) will be collected through active surveillance until the participant completes (or withdraws early from) the study.

This study will be conducted by Guizhou Center for Disease Control and Prevention, Sichuan Center for Disease Control and Prevention, and Hunan Provincial Center for Disease Control and Prevention.

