### (3) Per-protocol set for efficacy (PPE)

It includes the susceptible population in the PPS with negative PCR results at baseline (baseline IgG < 338 BAU/mL) with no evidence of infection within 7 days after vaccination. The PPE population is the primary analysis population for VE assessment 7 days post-vaccination.

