**(7) Immunogenicity per-protocol evaluable (I-PPE)**

It includes the susceptible population in the PPS with negative PCR results at baseline (baseline IgG < 338 BAU/mL). The I-PPE is the primary analysis population for immunogenicity. Particularly, for participants with evidence of SARS-CoV-2 infection, post-infection immunogenicity data will be excluded from analysis, and pre-infection immunogenicity data may still be included.

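### No stated rule ties the 200 persistence participants to baseline IgG or PCR, yet the SAP analyses persistence only in I-PPE and departs from the protocol's I-PPS

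*Combined protocol and SAP*

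**What the plan says.** **Who is sampled.** The protocol synopsis, under immunogenicity follow-up, states that "200 participants in the immunogenicity subgroup will be sampled on Days 7, 90, 180 and 365 for nAb of SARS-CoV-2", and Table 1 note 10 repeats this. SAP 4.1 describes the subgroup, "of which 200 participants need to undergo additional scheduled sampling on Day 7, Day 90 and other longer periods". The subgroup is 5% to 10% of the full analysis set (FAS). The only statement on its make-up is in the synopsis under Study Design: "No limitation for the type of COVID-19 vaccine previously received or age ranges". Baseline IgG and PCR are not mentioned.

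**Who is analysed.** SAP 7.6.2.2.2: "The immunogenicity analysis for the persistence will be based on subgroups of I-PPE that participate in the immune persistence study". SAP 6 (7) defines I-PPE: "It includes the susceptible population in the PPS with negative PCR results at baseline (baseline IgG < 338 BAU/mL"). For prime immunization, SAP 7.6.2.2.1 makes I-PPE the main set and also analyses I-PPS. The persistence section has no such second analysis.

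**What the protocol names.** Under statistical populations and immunogenicity analysis, the synopsis makes I-PPS the main set. Its definition carries no IgG limit and no baseline PCR condition. SAP 2.3 nevertheless declares the SAP consistent with the protocol. The SAP abbreviation list also contains an Immunogenicity Persistence Set (IPS), which SAP 6 never defines.

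**Why the two groups can differ.** Inclusion criterion 4 sets IgG below 338 BAU/mL as the default but allows the limit to be adjusted or dropped; in that case "the participants will be sampled during screening period without waiting for the result before enrollment". Table 1 note 4 lets vaccination proceed before the baseline nucleic acid report.

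**The concern.** The sampling rule and the analysis rule were written separately. Followed literally, anyone among the 200 with IgG of 338 or more, or a positive baseline PCR, gives blood at up to four extra visits and contributes nothing to the persistence analysis.

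Titers and seroresponse rates on Days 7, 90, 180 and 365 are named secondary endpoints in the protocol, and only these 200 people supply those days. The early-response and durability results could therefore rest on a fraction of the planned number. The comparison of positive rates, a CMH test using the randomization strata (age, vaccine type, site), would become sparse. Because the SAP uses a different main set from the protocol, it is also unclear which analysis the sponsor intends.

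**Working it through.** The plan gives no derivation or precision target for the 200, so there is no planned figure to reproduce. The check asks how many of the 200 could be in I-PPE.

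**Inputs**
- FAS: 9,196 (Table S1).
- IgG below 338: 3,288 of 9,191 with a result (Table S1).
- Baseline nucleic acid negative: 7,838 of 9,187 with a result (Table S1).
- PPE: 2,623 (Table S2).
- Assumption: the 200 resemble the FAS. No table describes the subgroup or the 200.

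**Bounds on the I-PPE share**
- Lower bound. PPE applies the I-PPE conditions and adds "with no evidence of infection within 7 days after vaccination. The PPE population is the primary analysis population for VE assessment 7 days post-vaccination". PPE is therefore the narrower set, and its share is a floor: 2,623 / 9,196 = 28.5%; 200 × 0.285 = 57.
- Upper bound. Everyone in I-PPE has IgG below 338: 3,288 / 9,191 = 35.8%; 200 × 0.358 = 72.
- Illustration. If IgG and PCR status were independent: (3,288 / 9,191) × (7,838 / 9,187) = 0.358 × 0.853 = 30.5%; 200 × 0.305 = 61.

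So 57 to 72 fall inside I-PPE, about 29 to 36 per arm instead of 100, and 64% to 71.5% fall outside. Drop-out and the removal of post-infection samples reduce this further at later visits.

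**Precision.** With the same standard deviation of log titer, interval width varies as 1/√n: √(200/57) = 1.87 and √(200/72) = 1.67. A group restricted to low baseline IgG may vary less, which would soften these ratios.

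**If the IgG limit had been enforced.** SAP 4.3 expects about 15% to be lost to baseline PCR positivity or infection in the first 7 days. That leaves 200 × 0.85 = 170, a width ratio of √(200/170) = 1.08. The problem is therefore mainly the waived IgG limit.

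**What I-PPS would recover.** I-PPS has no IgG limit, so participants at or above 338 return. Baseline PCR-positive participants may still drop out under the rules that remove infected participants or their post-infection data. In that case 200 × 0.853 = 171 remain before other exclusions.

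**Feasibility of selecting on I-PPE criteria.** Finding 200 eligible people needs a subgroup of 200 / 0.358 = 559 to 200 / 0.285 = 702, or 6.1% to 7.6% of 9,196. At 5% (460 people) only 460 × 0.285 = 131 to 460 × 0.358 = 165 would be eligible.

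**The case against.** The strongest reply is that the mismatch is read from silence. The protocol text available is the synopsis and schedule, which point to numbered sections (9.3.4 and 11.4.4) that are not included; a selection rule could sit in the full text. This stands as a limit: the documents do not show that the 200 were drawn without regard to baseline status, only that no visible rule links them to I-PPE.

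A reader might also infer that about 70% of the samples are wasted. The documents do not establish that. The shares come from results tables for the whole trial, not from planning text or from the subgroup. By default the plan enrols people below 338, and the waiver is conditional.

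Nor is it right that early response depends only on these 200, because Days 14 and 28 are sampled in the whole subgroup.

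Immunogenicity lies outside the test hierarchy (SAP 7.10), its P values are nominal, and the plan never sets 200 evaluable as a target. This limits the consequence to precision and interpretability. Finally, under the protocol's own I-PPS the participants with high IgG would be analysed, so the loss comes from the SAP's choice of set. That is correct, and it points to the simplest remedy.

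**Conclusion.** The concern holds as a mismatch between sampling and analysis, together with an undeclared departure from the protocol's immunogenicity set. On the assumption that the 200 resemble the FAS, 57 to 72 of them enter the persistence analysis before drop-out and infection exclusions, with intervals roughly 1.7 to 1.9 times wider than with 200 evaluable. The figure depends on how the 200 were actually chosen, which the available text does not say. The primary efficacy conclusion and the tested hierarchy are unaffected. The point is still worth correcting, because people give blood for named secondary endpoints under a plan that may not use the samples.

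**What to change.** (a) In SAP 7.6.2.2.2, add I-PPS as a persistence analysis, as SAP 7.6.2.2.1 already does. State which set is the main one, reconcile it with the protocol's I-PPS, and either record the change in SAP 2.3 or remove it. Say how participants who are PCR positive at baseline are handled, and define IPS or delete it. The cost is wording and one more set of tables; nobody is sampled differently.

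(b) If I-PPE stays the main persistence set and selection is still open, amend the synopsis, Table 1 note 10 and SAP 4.1 so that the 200 are filled, balanced by arm through the IWRS, from subgroup members with a negative baseline PCR and IgG below 338. Both are measured on samples taken before vaccination, so selecting on them does not bias the arm comparison. Set the subgroup at about 6% to 8% of the FAS or more, which is within the planned 5% to 10%; the 5% end would fall short. If results are late, take the Day 7 sample and apply the rule before Day 90.

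The costs of (b) are an IWRS flag and extra Day 7 draws. If no result were back in time, these would number at worst about 559 − 200 = 359 to 702 − 200 = 502. There would also be no antibody data at the extra visits, including the long-term ones, in people with IgG of 338 or more.

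If selection is already complete, do (a), state how the 200 were chosen, and report by arm and visit how many are in I-PPE and in I-PPS.

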### **7.7 Safety evaluation**

#### **7.7.1 AEs**

AEs are coded using MedDRA (V25.1\_Chinese version), and classified and counted according to the System Organ Class (SOC) and Preferred Term (PT). In addition, solicited AEs will be categorized by local AEs and systemic AEs specified in the protocol.

The number of participants and incidence of AEs in each group are calculated as follows:

- All AEs;
- AEs related to the study vaccine;
- AEs with an incidence of  $\geq 0.1\%$  in any group;
- AEs related to the study vaccine with an incidence of  $\geq 0.1\%$  in any group;
- AEs with an incidence of  $\geq 1\%$  in any group;

- AEs related to the study vaccine with an incidence of  $\geq 1\%$  in any group;
- AEs with an incidence of  $\geq 10\%$  in any group;
- AEs related to the study vaccine with an incidence of  $\geq 10\%$  in any group;
- AEs of different severity (Grade 1, Grade 2, Grade 3, Grade 4, Grade 5,  $\geq$  Grade 2, and  $\geq$  Grade 3);
- AEs related to the study vaccine of different severity;
- AEs by occurring time (within 30 min, 0–7 days, 0–14 days, 8–28 days);
- AEs related to the study vaccine with different onset times;
- AEs leading to withdrawal;
- AEs related to the study vaccine leading to withdrawal.

The severity and the relatedness to the study drug of the AEs are described statistically.

A list of adverse events is provided.

#### **7.7.2 SAEs**

The number of participants and incidence of SAEs in each group are calculated as follows:

- All SAEs;
- SAEs related to the study vaccine;
- SAEs related to the study vaccine with severity  $\geq$  Grade 3;

A list of SAEs is provided.

#### **7.7.3 AESIs**

The number of participants and incidence of AESIs in each group are calculated as follows:

- All AESIs;
- AESIs related to the study vaccine;

A list of AESIs is provided.

### **7.8 Handling of missing data**

In the evaluation of protective efficacy post vaccination, if the participant misses a follow-up, he/she will be considered non-infected for that follow-up to evaluate the protective efficacy.

In the study, the missing data of the safety evaluation endpoints and immunogenicity endpoints are not processed.

### **7.9 Subgroup analysis**

If data permit, the following subgroups will be analyzed separately for protective efficacy and

immunogenicity:

- Age (18–59 years,  $\geq 60$  years)
- Sex (male, female)
- Time since last previous vaccination (6–12 months, 13–24 months)
- Vaccine type of the last previous dose (inactivated, non-inactivated)

In particular, if the model does not converge due to too few observed events during subgroup analysis, the factor of groups is only retained in the subgroup analysis model.

## 7.10 Multiplicity

The overall Type I error of the study will be controlled to a one-sided 0.025 using a hierarchical test in a fixed sequence as follows:

- (1) Primary endpoint: VE  $> 30\%$  against symptomatic infection of SARS-CoV-2 after 7 days post vaccination ( $\geq 8$  days) in PPE population;
- (2) Secondary endpoint: VE  $> 0\%$  against obvious symptomatic infection of SARS-CoV-2 after 7 days post vaccination ( $\geq 8$  days) in PPE population;
- (3) Secondary endpoint: VE  $> 0\%$  against all infections of SARS-CoV-2 after 7 days post vaccination ( $\geq 8$  days) in PPE population;
- (4) Secondary endpoint: VE  $> 0\%$  against symptomatic infection of SARS-CoV-2 after 14 days post vaccination ( $\geq 15$  days) in PPE-14 population;
- (5) Secondary endpoint: VE  $> 0\%$  against obvious symptomatic infection of SARS-CoV-2 after 14 days post vaccination ( $\geq 15$  days) in PPE-14 population;
- (6) Secondary endpoint: VE  $> 0\%$  against asymptomatic SARS-CoV-2 infection after 7 days post vaccination ( $\geq 8$  days) in PPE population;
- (7) Secondary endpoint: VE  $> 30\%$  against obvious symptomatic infection of SARS-CoV-2 after 7 days post vaccination ( $\geq 8$  days) in PPE population;
- (8) Secondary endpoint: VE  $> 30\%$  against all infections of SARS-CoV-2 after 7 days post vaccination ( $\geq 8$  days) in PPE population;
- (9) Secondary endpoint: VE  $> 30\%$  against symptomatic infection of SARS-CoV-2 after 14 days post vaccination ( $\geq 15$  days) in PPE-14 population;
- (10) Secondary endpoint: VE  $> 30\%$  against obvious symptomatic infection of SARS-CoV-2 after 14 days post vaccination ( $\geq 15$  days) in PPE-14 population.

In the other endpoints of efficacy, immunogenicity and safety, the calculated P value is just a nominal P value; it is mainly used to describe association strength between the endpoints and treatment subgroups, and is not used as the basis for formal statistical inference.

